## Abstract

**Background:**

Smokers need effective support to maximise the chances of successful quit attempts. Current smoking cessation medications, such as nicotine replacement therapy (NRT), bupropion, nortriptyline or varenicline, have been shown to be effective in clinical trials but are underused by smokers attempting to quit due to adverse effects, contraindications, low acceptability and/or high cost. Cytisine is a low-cost, plant-based alkaloid that has been sold as a smoking cessation aid in Eastern Europe for 50 years. A systematic review of trial evidence suggests that cytisine has a positive impact on both short- and long-term abstinence rates compared to placebo. However, the quality of the evidence is poor and insufficient for licensing purposes in many Western countries. A large, well-conducted placebo-controlled trial (n = 740) of cytisine for smoking cessation has recently been published and confirms the findings of earlier studies, with 12-month continuous abstinence rates of 8.4% in the cytisine group compared to 2.4% in the placebo group (Relative risk = 3.4, 95% confidence intervals 1.7-7.1). No research has yet been undertaken to determine the effectiveness of cytisine relative to that of NRT.

**Methods/design:**

A single-blind, randomised controlled, non-inferiority trial has been designed to determine whether cytisine is at least as effective as NRT in assisting smokers to remain abstinent for at least one month. Participants (n = 1,310) will be recruited through the national telephone-based Quitline service in New Zealand and randomised to receive a standard 25-day course of cytisine tablets (Tabex^®^) or usual care (eight weeks of NRT patch and/or gum or lozenge). Participants in both study arms will also receive a behavioural support programme comprising an average of three follow-up telephone calls delivered over an eight-week period by Quitline. The primary outcome is continuous abstinence from smoking at one month, defined as not smoking more than five cigarettes since quit date. Outcome data will also be collected at one week, two months and six months post-quit date.

**Discussion:**

Cytisine appears to be effective compared with placebo, and given its (current) relative low cost may be an acceptable smoking cessation treatment for smokers, particularly those in low- and middle-income countries. Cytisine's 'natural' product status may also increase its acceptability and use among certain groups of smokers, such as indigenous people, smokers in countries where the use of natural medicines is widespread (e.g. China, India), and in those people who do not want to use NRT or anti-depressants to help them quit smoking. However it is important to ascertain the effectiveness of cytisine compared with that of existing cessation treatments.

**Trial registration:**

Australian New Zealand Clinical Trials Registry (ACTRN12610000590066)

## Background

One in two smokers will die of a smoking-related disease, and half of those who die as a direct consequence of smoking will die in middle age [1]. Smoking (combining active and passive smoking) is responsible for approximately 18% of all deaths in New Zealand [2], an island nation (population 4.3 million) in the Southwest Pacific. Smoking contributes substantially to the life expectancy differential between Māori (indigenous New Zealanders who comprise 15% of the national population) and non-Māori [3]. Stopping smoking at any age reduces smoking related risks and increases life expectancy [4]. Effective treatments to aid smoking cessation have clear individual and public health benefits and provide the most efficient use of health care resources at a population level [5].

Use of pharmacological treatments such as nicotine replacement therapy (NRT), bupropion and nortriptyline approximately doubles a smoker's chance of long-term abstinence [6,7]. Varenicline appears superior to bupropion and at least doubles the long-term chances of quitting compared to placebo [8]. The success of a smoking cessation product depends on its availability and acceptability to smokers as well as its efficacy. In 2009 in New Zealand, among smokers aged 15-64 years who had made a recent quit attempt, 22% had used NRT and 4.6% had used a prescription medicine (e.g. varenicline) to support their quit attempts [9]. Many smokers are misinformed about the risks of nicotine and are therefore hesitant to use NRT [10,11]. Bupropion and nortriptyline have a number of adverse effects and contraindications [7], which may contribute to their relatively poor uptake among smokers trying to quit. Given these issues new pharmacological treatments to help people quit smoking need to be identified - one such product is cytisine.

Cytisine is an alkaloid found in plants such as the Golden Rain tree (*Cytisus laburnum*) [12] and the New Zealand Kowhai tree (*Sophora tetraptera*) [13]. Such plants are considered to be poisonous to humans, with the alkaloids they contain (including cytisine) considered to be the toxic components. However, an oral tablet form of cytisine, Tabex^®^, has been marketed by Sopharma (Bulgaria) as a smoking cessation aid since the 1960's. When used at its therapeutic dose (1.5-9 mg of cytisine per day) trial data indicates that Tabex^® ^is well tolerated with few adverse effects, similar to those seen with NRT use [14-17]. Furthermore, West et al. (2011) report that a recent Periodic Safety Update provided to European authorities, did not identify any safety signals for cytisine (based on a sample of more than 7 million exposed persons) [17]. Cytisine overdose has been reported and is likened to nicotine intoxication, with symptoms including nausea, vomiting, pupil dilation, tachycardia, general weakness, clonic convulsions, and respiratory paralysis [18]. Cytisine is off-patent and currently relatively inexpensive compared with most other pharmacological cessation products on the market. Cytisine may also be attractive to those people who prefer not to use a nicotine-based product or antidepressants to help them quit smoking. A recent qualitative study looking at cytisine's potential to be used as a healing remedy by traditional indigenous healers to help their people stop smoking, suggests that cytisine would be very attractive if it were marketed in a culturally appropriately manner [19].

Like its analogue varenicline, cytisine acts as a partial agonist of the nicotinic acetylcholine receptor [8]. It is thought to aid smoking cessation by reducing the reward and satisfaction associated with smoking [20]. Despite having been used by hundreds of thousands of smokers throughout Eastern Europe [20], cytisine is rarely mentioned in English-language literature and there are only limited data from clinical trials to support its use. A systematic review [14] identified three placebo-controlled trials of cytisine and all were published in non-English language journals. All three trials were conducted over 30 years ago in Eastern Europe prior to the advent of good clinical practice (GCP) guidelines and all suffered from weaknesses in study design and reporting of results [21-23]. The authors of the review combined data from these trials in a meta-analysis and reported a clear effect on smoking abstinence at 3-8 weeks (Odds Ratio [OR] 1.93, 95% confidence interval [CI] 1.21 to 3.06) and at 3-6 months (OR 1.83, 95% CI: 1.21 to 2.99) for cytisine compared to placebo [14]. Although these findings appear promising, the three trials were not conducted to GCP standards and thus regulatory authorities in many countries are unlikely to accept the evidence for licensing purposes. Data from at least two appropriately powered placebo-controlled clinical trials run to GCP standards are required to satisfy regulatory authorities in most western countries. Since the review was published, two additional placebo-controlled trials of cytisine have been published and both confirm earlier findings [16,17]. The first trial was well-conducted, with randomisation, double-blinding and clear outcome measures, but was underpowered (n = 171). The authors reported an OR for cessation at 26 weeks of 8.93 (95% CI: 1.06 to 75.28). A second trial had a large sample size (n = 740), was conducted to GCP standards and reported 12-month continuous abstinence rates of 8.4% in the cytisine group compared to 2.4% in the placebo group (relative risk=[RR] 3.4, 95% CI 1.7-7.1) [17].

Following on from the recently published placebo-controlled trial by West et al. (2011) [17], an appropriate research question to now answer is how the efficacy of cytisine compares to NRT. Such a question is important from a policy and funding perspective to help decide whether to use cytisine as a first or second line agent for smoking cessation treatment or whether to publicly fund the drug. Based on the systematic review mentioned above, the expected difference in efficacy between cytisine (OR = 1.83, 95% CI 1.21 to 2.99)[14] and NRT (OR = 1.74, 95% CI 1.64 to 1.86) [6] is too narrow to feasibly conduct a head-to-head superiority trial. We therefore propose conducting a non-inferiority trial to demonstrate whether cytisine is at least as effective as NRT at increasing quit rates in dependent smokers motivated to quit.

### Objectives

The primary objective of the trial is to determine how effective cytisine is at increasing quit rates at four weeks after randomisation. This study has three main hypotheses: 1) that cytisine plus behavioural support is at least as effective as usual care (NRT plus behavioural support) at increasing quit rates; 2) that cytisine plus behavioural support is at least as effective as usual care (NRT plus behavioural support) at reducing the severity of withdrawal symptoms; and 3) that cytisine is an acceptable smoking cessation treatment to Māori, Pacific and non-Māori non Pacific alike.

## Methods/Design

### Study design

This study is a parallel group, single-blind, non-inferiority, randomised controlled clinical trial.

### Study population

The study population will be registered and eligible callers to the national toll-free smoking cessation helpline [Quitline] in New Zealand.

### Inclusion criteria

Participants will be smokers from throughout New Zealand who want to stop smoking, are at least 18 years of age, are able to provide verbal consent, and have access to a telephone.

### Exclusion criteria

Pregnant women and women who are breastfeeding will be excluded from the trial. People will also be excluded from the trial if they meet any of the following criteria: current users of pharmacological cessation therapies (e.g. NRT, buproprion, clonidine, nortriptyline or varenicline); current clients of another smoking cessation programme or cessation study; they have uncontrolled high blood pressure (> 150 mmHg systolic, > 100 mmHg diastolic), schizophrenia or phaeochromocytoma; they have had a myocardial infarction, angina, severe cardiac arrhythmia or a stroke in acute phase within the last two weeks. The medical conditions above are listed contraindications for the use of cytisine, NRT patch, gum, and lozenge. A number of disease conditions are known where precautions for the use of NRT products are indicated, and will be assessed in each participant by researchers prior to randomisation. These include: severe cardiovascular disease (occlusive peripheral arterial disease, cerebrovascular disease, stable angina pectoris, and uncompensated heart failure) and vasospasm, uncontrolled hypertension, renal or hepatic impairment, active duodenal ulcers and gastric ulcers.

### Randomisation: allocation concealment and sequence generation

All participants will be assigned a unique registration number allocated by a central computer following details submitted on a web-based form. This number will be used to identify each randomised participant who has consented to take part. Participants will be randomised by computer, with stratified minimisation by sex, ethnicity (Māori, Pacific, non-Māori non-Pacific), and level of nicotine dependence (> 5 points, ≤ 5 points on the Fagerström Test for Nicotine Dependence [FTND] questionnaire [24]), to ensure a balance in these key prognostic indicators between the intervention and control groups. The randomisation sequence will be concealed from all research staff and will not be able to be manipulated.

### Blinding

Due to the nature of the intervention only single blinding (of researchers, not of participants) is possible. Members of the trial steering committee, management committee, and other study team members (with the exception of the project co-ordinator and the Quitline senior research manager) will remain blinded to treatment allocation until the code is broken (namely, after the last follow-up call is completed and the data recorded). The project co-ordinator will not be blinded as they will be responsible for distributing the cytisine to participants. The senior research manager and research assistants based at Quitline will not be blinded to treatment allocation, as they are required to know which group each participant has been allocated to in order to conduct the scheduled follow-up calls.

### Study intervention

Participants will be randomised to receive a course of cytisine [intervention] or usual care [control] (Figure 1). All participants will also receive an eight week, telephone-based, behavioural support programme delivered by Quitline advisors. Quitting support generally involves an average of three follow-up telephone calls, each lasting about 10-15 minutes. However, if people do not want to receive this support, they are not scheduled and callers are advised that they can phone Quitline at any time for support.

**Figure 1 F1:**
[figure not shown]
**Trial schematic**. Footnote: NRT = Nicotine replacement therapy.

#### Intervention

Participants in the intervention arm will receive a 25-day course of cytisine tablets (Tabex^®^) delivered by courier. Participants will be asked to reduce their smoking over the first four days of treatment so that they are not smoking at all by the fifth day, which will be their designated Quit date. Participants will follow the dosing regimen as recommended by the manufacturer, namely:

• Days 1-3: 1 tablet every 2 hours through the waking day (up to six tablets per day)

• Days 4-12: 1 tablet every 2.5 hours (up to 5 per day); designated Quit date is day 5

• Days 13-16: 1 tablet every 3 hours (up to 4 per day)

• Days 17-20: 1 tablet every 4-5 hours (3 per day)

• Days 21-25: 1 tablet every 6 hours (2 per day)

As part of an automated process at Quitline, all participants, including those in the treatment group, will be sent Quitcards, which may be redeemed for subsidised NRT (see below for more detail). However, participants will be asked to use the cytisine tablets sent to them for the first 25 days, and not the NRT. Participants will be told to redeem their vouchers for NRT only if they are smoking one month after their trial quit date or require on-going cessation support after they have finished the course of cytisine.

#### Control

Participants allocated to the control arm of the trial will be asked to stop smoking completely on their chosen Quit date and will be supported by Quitline in the usual way for eight weeks, with counselling/advice and NRT in the form of a patch and/or gum or lozenge. Current standard cessation practice at the New Zealand Quitline (as at November 2011) is as follows (other cessation providers in New Zealand do not follow the process outlined here): Quitline issues by post, two (or sometimes three) four-week Quitcards (with a 90 day expiry). Participants take each four-week Quitcard to a pharmacist in exchange for subsidised patches and/or gum or lozenges (NZ$3-6 per item per four-week course of NRT). The strength of NRT patch and/or gum or lozenges to be used by each participant is determined by the Quit advisor (as per their dosage guidelines) as to the degree of each person's nicotine dependency.

### Baseline assessments

Participants from throughout New Zealand will call Quitline seeking advice and wishing to enrol in the Quitline smoking cessation programme. A Quit advisor from Quitline will undertake the standard Quitline assessment. A list of those individuals who indicate "yes" to taking part in research will be transferred from the Quitline database to the research assistants based at Quitline. The research assistants will attempt to make contact with people on the list. Those contacted will be told about the trial and will be asked if they would like to take part in the study. If the potential participant indicates that they are interested, they will be consented and asked for demographic data (age and sex) and checked to see if they meet the inclusion criteria for the trial. For those who do meet the inclusion criteria, further details will be collected about the participant's ethnicity and level of nicotine dependence (as determined by the FTND [24]) and they will be randomised. Data from this initial assessment will then be electronically transferred (securely) to the Clinical Trial Research Unit's Oracle database. The research assistant will then collect the following baseline data from each participant over the telephone.

• *Demographic information: *Socio-economic position based on education.

• *Smoking history: *Age when started, number of cigarettes smoked per day, number of years as regular smoker, number of previous unsuccessful attempts to give up in past 12 months and the method used, type of cigarettes smoked per day (e.g. roll-your-own or factory-made) and usual brand/pack size (and how long pack lasts for roll-your-own users).

• *Other smoking related information: *Self-rated chances of quitting, household smoking, and smoking in cars. Satisfaction with smoking will also be assessed at baseline (and at follow-up), using the modified Cigarette Evaluation Questionnaire (mCEQ) [25]. This questionnaire was used in the one trial (n = 746) that has compared the effect of varenicline versus NRT on quit rates [26]. This trial found varenicline use resulted in significantly less satisfaction with smoking compared to NRT use, in those participants that did not quit smoking. It is important to determine if cytisine, given it is a similar class of drug to varenicline, has an analogous effect.

• *Concomitant medication: *Information about types of medication currently used will be collected.

• *The physical signs and symptoms associated with withdrawal: *Measured using the Mood and Physical Symptoms Scale (MPSS) [27].

• *Alcohol use and abuse: *Data from both animal [28] and human studies [29] have shown that varenicline can also reduce alcohol consumption. Given cytisine is a similar class of drug as varenicline it may have an analogous effect on alcohol use, although to date no such effect has been published. For this reason, information about alcohol use and abuse will be collected in this study, using the Alcohol Use Disorders Identification Test-consumption subscale [AUDIT-C], a screening tool that helps to identify people who are hazardous drinkers or have an active alcohol use disorder (including alcohol abuse or dependence) [30].

### Outcome measures

#### Primary outcome

The proportion of participants that have stopped smoking, one month post-quit. 'Stopped smoking' will be defined as self-report of having smoked not more than five cigarettes in the one month after the Quit date (continuous abstinence).

#### Secondary outcome

The following secondary outcome measures will be assessed at one week and one month after the Quit date in the treatment group only:

• *Information related to the use of cytisine: *Participants will be asked for their views on the use of cytisine as a cessation aid (i.e. whether they would recommend the treatment to another smoker and whether they liked or disliked using the product).

• *Participants' treatment compliance: *Self-reported pill counts (also asked at two months), concomitant cytisine and NRT use (also asked at two months), early stopping of cytisine and reasons why.

The following secondary outcome measures will be assessed in all participants at one week and one, two and six months after the Quit date:

• *The physical signs and symptoms associated with withdrawal: *Assessed using the MPSS [27] in abstinent smokers, measured at one week, one month and two months only.

• *Self-rated chances of quitting: *Measured at one week, one month and two months only.

• *Seven-day point prevalence: *The proportion of participants that have stopped smoking, defined as self-report of having smoked no cigarettes (not even a puff) in the past seven days. Measured at every time point.

• *Continuous abstinence: *The proportion of participants that have stopped smoking, defined as self-report of smoking not more than five cigarettes from the Quit date. Assessed at every time point.

• *Use of cigarettes: *If the participant is smoking at any time point, the following outcomes will be assessed: number of cigarettes smoked per day; proportion of participants who have significantly reduced their daily smoking level (defined as reducing consumption by at least 25% in terms of numbers of cigarettes per day or weight of loose tobacco per day); smoking satisfaction (measured using the mCEQ).

• *Use of NRT: *All participants will be asked about use of any NRT (including type, dosage, flavour, and frequency of use) at every time point.

• *Use of non-NRT methods of cessation: *Participants will be asked about their use of non-NRT methods of cessation such as buproprion, clonidine, nortriptyline, varenicline, acupuncture etc, measured at two and six months only.

• *Alcohol use and abuse: *Measured using the AUDIT-C. Measured at one and two months only.

• *Adverse events: *Information regarding any adverse events and whether they are considered to be related to treatment will be collected at every time point.

• *Cost information: *Cost outcomes will be derived from known costs of the various products, and will include cost per quitter and cost per person reducing their daily cigarette consumption. The tobacco expenditure savings to individual smokers will also be calculated using data on the daily amount smoked prior to quitting and the price of the particular products smoked.

• *Concomitant medication: *Collected at every time point.

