A pre-analysis review will be conducted before the primary analyses. The purpose of this review is to establish rules for a per protocol analysis and to reconsider the analysis plan (e.g., adjustment for potential confounders) in light of recent research. Any amendments (and the rationale) will be justified and documented in the statistical analysis plan. A per protocol analysis involves looking at the major protocol violations such as cross-over treatments, withdrawals and lost to follow-up. The per protocol population will consist of all randomized patients who have complied with the treatment allocated, were not lost to follow-up, and who do not have major protocol deviations pertaining to eligibility or the assessment of the treatment difference.

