#### Tolerability

All randomised participants who receive at least one dose of intervention or control treatment will be included in the planned analyses. Comparison of the frequency of treatment withdrawal between the intervention and the control group will be tested using Chi-square statistics. The numbers of participants discontinuing treatment prematurely for any reason will be summarised by treatment group and by reasons for discontinuation. The incidence of all suspected serious adverse treatment reactions will be summarised by treatment group.

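### Early stopping and its reasons are listed for the cytisine arm only, yet the tolerability analysis compares withdrawal between arms, over courses of unequal length and with no stated window

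*Protocol article*

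**What the plan says.** In the protocol article, Secondary outcome lists two blocks of measures. The first, which "will be assessed at one week and one month after the Quit date in the treatment group only", holds the compliance items: self-reported pill counts and "concomitant cytisine and NRT use (also asked at two months), early stopping of cytisine and reasons why". The second block covers all participants and includes "All participants will be asked about use of any NRT (including type, dosage, flavour, and frequency of use) at every time point". Adverse events and their relation to treatment are also recorded for everyone at each call.

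Two analyses draw on these data.

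- Tolerability: "Comparison of the frequency of treatment withdrawal between the intervention and the control group will be tested using Chi-square statistics". The numbers "discontinuing treatment prematurely for any reason will be summarised by treatment group and by reasons for discontinuation" are also promised.
- Treatment effects: the per-protocol population is "all randomized patients who have complied with the treatment allocated", with further conditions on follow-up and major deviations. The detailed rules are left to a pre-analysis review.

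The cytisine course is 25 days with the Quit date on day 5 (Intervention). The control course of NRT and support is eight weeks (Control).

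**The concern.** The outcome list assigns the early-stopping items to one arm, and the tolerability analysis needs them in both. This is more than an omission from a condensed article. The article states that the items belong to the treatment group only, and then states an analysis that needs the same information from controls. If the list is followed as written, the control column of the table by reason has no dedicated source.

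A second problem would remain even with complete data. The chi-square test has no stated window. If stopping is counted over each arm's whole course, NRT users have more than twice as long in which to stop, and the test could show cytisine as better tolerated only because its course is shorter.

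**Working it through.** **1. What each analysis needs and where it could come from** (protocol article, Secondary outcome)

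| Needed | Cytisine arm | Control arm |
|---|---|---|
| Still using the allocated product at each call | Early-stopping item, pill counts | NRT-use item asked of everyone (coarse) |
| When treatment stopped | Early-stopping item and pill counts | No listed item; only between which two calls |
| Why treatment stopped | "early stopping of cytisine and reasons why" | No listed item; adverse events cover part |
| Compliance for the per-protocol set | Pill counts | NRT-use item (coarse) |

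The gap is therefore the stop date and the reason in controls. Current use and a coarse compliance measure are available in both arms.

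**2. The plan's own figure**

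The plan gives no number on this point. The only planning figure used below is the group size. With 50% v 55%, a 5-point margin, one-sided 0.025 and 90% power (Sample size):

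(1.960 + 1.282)² × (0.50 × 0.50 + 0.55 × 0.45) / 0.10² = 523 per group, and 523 / 0.80 = 654, against the stated 655. It reproduces.

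**3. Unequal time at risk**

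Inputs from the documents: 25 days (Intervention) and 8 × 7 = 56 days (Control). Assumption: the same constant daily stopping hazard in both arms. If a proportion p has stopped by day 25, the proportion stopped by day 56 is 1 − (1 − p)^(56/25), with 56/25 = 2.24. The values of p are illustrative.

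| Stopped by day 25 | Stopped by day 56 | Gap |
|---|---|---|
| 10% | 21% | 11 points |
| 20% | 39% | 19 points |
| 30% | 55% | 25 points |

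For the smallest gap, with 655 per group and the pooled variance that matches a chi-square test: pooled p = (0.100 + 0.210)/2 = 0.155; SE = √(0.155 × 0.845 × 2/655) = 0.0200; z = 0.110/0.0200 = 5.5. Under this assumption, a whole-course test would be strongly positive with no difference in the tendency to stop.

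The Discussion (Primary outcome assessment) describes the cytisine course as 28 days, against 25 days in the Abstract and Intervention sections. The passages must be reconciled. With 28 days the first row becomes 1 − 0.90^(56/28) = 19% instead of 21%, so the conclusion does not depend on it.

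**4. What the scheduled calls allow**

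Day 25 of cytisine falls 25 − 5 = 20 days after the Quit date. By the one-month call the cytisine course is over, while an eight-week NRT course is about half done. A comparison restricted to the period before that call is therefore possible within the existing schedule.

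**The case against.** The strongest reply is that the data are less one-sided than the list suggests. NRT is the allocated treatment for controls, and its use is asked of everyone at one week and at one, two and six months. A control reporting no NRT use at a call can be identified as having stopped. The Withdrawal criteria apply to both arms and keep follow-up calls going after treatment stops. A condensed article may also leave questionnaire items to the full protocol or case record form. On the window, the Tolerability section does not say that whole courses will be compared, and comparing each regimen over its own course is a legitimate question.

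Much of this stands. A reader might infer that a per-protocol set with the same kind of rule in both arms cannot be built. The documents do not support that: the definition covers both arms, the NRT-use answers supply a control measure, and the pre-analysis review can set a common rule. A reader might also infer that the per-protocol result will be biased towards cytisine because only cytisine users are screened out. That would require no exclusions among controls, which the protocol does not plan. What can be said is that compliance is measured more finely in one arm than in the other.

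The reply does not supply controls' reasons for stopping. Adverse-event records would miss someone who stops NRT because of relapse, cost or dislike, and the Withdrawal criteria name no item that records a control participant's own decision to stop. Nor does it supply a window. The pre-analysis review can choose a rule, but it cannot recover answers that were never asked for.

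**Conclusion.** The point holds as an inconsistency between Secondary outcome and Tolerability. Early stopping and its reasons are listed for cytisine only, while the analysis compares withdrawal between arms and tabulates reasons by arm. Control stopping can be derived coarsely, to within the interval between calls. Control stop dates and reasons have no listed source.

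The missing window is a second, smaller defect. Its illustrated size is 11 to 25 points for 10% to 30% stopped by day 25. This rests on an equal, constant hazard and on counting over whole courses, neither of which the documents establish. It shows how far the choice of window could drive the result and is not a forecast.

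The main consequence is for a secondary tolerability comparison. The intention-to-treat primary analysis is not affected. The per-protocol analysis is feasible, but needs one rule for both arms. The change is worth making because it is cheap and the information is lost if not collected at the calls.

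**What to change.** - **Secondary outcome:** ask both arms at the existing one-week, one-month and two-month calls whether the allocated product is still being used, the date it was stopped and the reason.
- **Tolerability:** compare discontinuation over a common window counted from the start of treatment, for example the first 25 days, or by time to discontinuation. Report completion of each whole course descriptively. Reconcile the 25-day and 28-day descriptions of the cytisine course first, since the window depends on them.
- **Treatment effects (per-protocol population):** state the control compliance measure, and apply one compliance rule to both arms over the same period, up to the one-month call.

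The cost is two or three extra questions to control participants in calls already made, plus wording in the analysis plan. Recruitment began on 1 April 2011 (Current status), so controls already past these calls would have only the coarse NRT-use answers. The report should say how many that is. If the full protocol or case record form already carries these items for controls, correcting the outcome list and stating the window and the compliance rule is enough.
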